12.2.1 Obstetrical

Prenatal:

• Late miscarriage occurred between 16 and 22 weeks

• Premature delivery  34, 32, 28 SA.

• Hospitalization for the threat of premature labor

• Number of days of hospitalization for threat of preterm birth

• Premature rupture of the membranes before 37 SA

• Occurrence of chorioamnionitis defined by two of the following criteria: maternal temperature> 38 ° C, uterine contractions, foul leucorrhea, fetal tachycardia> 160 bpm, CRP> 10 mg / L.

During work :

• Hyperthermia> 38 ° C

• Fetal tachycardia> 160 bpm

In the postpartum:

• Hyperthermia> 38 ° C for more than 24 hours

• Need for antibiotic treatment for more than 48 hours

Neonatal 12.2.2

12.2.2.1 Neonatal mortality

• Early neonatal mortality from D0 to D6

• Late neonatal mortality from D7 to D28.

12.2.2.2 Neonatal morbidity

Immediate neonatal condition

Immediate neonatal status will be judged on the Apgar score, cord pH and transfer to neonatal resuscitation or ICU.

Neonatal infection:

It is most often caused by group B streptococci or Escherichia coli and may increase the risk of ventricular leukomalacia and bronchopulmonary dysplasia when it follows inflammation in utero 35. Clinical expression of infection in the new is not polymorphic. Any anomaly of the clinical examination that does not fit into evidence in another pathology will be considered as a sign of infection: respiratory distress not related to a resorption disorder or hyaline membrane disease, haemodynamic disorders, abnormality neurological examination.

The biological parameters studied will be, peripheral cultures, central crops, CRP (positive if greater than or equal to 10 mg / l), leukocytosis (positive if greater than 25000 or less than 5000) .These results are based on examinations systematically performed in the newborn. No further review will be conducted for this research on newborns.

We will consider as:

• Certain infection: Peripheral or central positive specimens and elevated CRP greater than 10 mg / l

• A probable infection: An abnormal clinical examination attributable to an infection or context of maternal chorioamnionitis and a CRP elevation greater than 10 mg / l.

Failure to meet the criteria listed above will cause the newborn to be uninfected.

Respiratory morbidity:

• Immediate:

• Transient respiratory distress

• Hyaline membrane disease

• Late :

• Oxygen dependence at 28 days

• Oxygen dependence at 36 SA

Cerebral morbidity

• Intra-ventricular hemorrhage grade 1-2-3-4 according to the criteria of Papile 36

• Periventricular leukomalacia

Digestive morbidity

• Occurrence of ulcerative necrotizing enterocolitis according to Bell's classification 37.

3 Practical realization of the study (Appendix I)

13.1 Inclusion of Patients and Inclusion File Filling: Role of Investigator and Clinical Research Technician

Participation in the research will be proposed to patients who will present themselves in the investigative departments for the realization of an amniocentesis between 15 and 20 AS for a prenatal diagnosis. All criteria will be verified by the investigating physician of the center.

Patients who meet all the inclusion criteria will be offered the opportunity to participate in the PREMYC trial.

The course of the study will be explained to the patient (information leaflet). The physician in charge of amniocentesis will collect a part of the informed consent signed by himself and by the patient. It will be made clear to the patient that she may refuse to participate in the trial, or withdraw her consent during the course of the study, without her care and relations with her doctor being affected.

At inclusion, the physician will complete the patient's inclusion sheet on a secure electronic CRF ("cleanweb" software).

This initial seizure will signal the inclusion of the patient in the clinical research technician who will then be responsible for entering patient data during the study.

The use of this computerized electronic FIU directly accessible via the Internet will facilitate interaction between the clinical centers, the bacteriology laboratory, the Henri Mondor CRU and the DRCD. In addition, a large part of the seizure can be done centrally by the clinical research technician. Finally, much of the monitoring by the Clinical Research Associate can be done centrally.

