16.3 Data Analysis

The data capture will be carried out as and when under the responsibility of the investigator through the software "cleanweb". The computer file will be processed under STATA (College Station, TX, USA)

Data analysis will be done in INSERM unit U149 by [name] and [name].

The study will distinguish 3 groups of patients according to the studied factor and the prescription of an antibiotic treatment: with a negative PCR, with a positive PCR without antibiotic treatment, with a positive PCR with antibiotic treatment.

These groups will be compared to each other for

• Clinical criteria collected at baseline: maternal age and level of education, obstetrical history, gestational age at baseline.

• Criteria collected during pregnancy: number of consultations, treatment, concomitant treatments, protocol outputs, adverse events and unblinding.

Then, an intention to treat the existence of an "antibiotic" effect in the form of a difference, in the case of a positive PCR, between the "placebo" group and the "josamycin" group for the main endpoint and the criteria of secondary judgments.

Comparisons will use non-parametric statistical tests whenever staffing or distribution constraints require it. For categorical variables, the chi2 test and the Fisher test will be used. Variance analysis and Kruskal and Wallis nonparametric testing will be used for continuous variables.

The effects will be measured as relative risk, with their 95% confidence interval.

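### The 'certain' neonatal infection class treats a peripheral culture as equal to a central one, so it mixes centrally confirmed infection with peripheral culture plus raised CRP

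*Protocol*

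**What the plan says.** Section 12.2.2.2 of the Protocol (Neonatal morbidity) sorts newborns into three classes.

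- *Certain*: "Certain infection: Peripheral or central positive specimens and elevated CRP greater than 10 mg / l".
- *Probable*: "An abnormal clinical examination attributable to an infection or context of maternal chorioamnionitis and a CRP elevation greater than 10 mg / l".
- Everyone else: "Failure to meet the criteria listed above will cause the newborn to be uninfected".

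The same section names the two culture types as separate parameters ("peripheral cultures, central crops, CRP (positive if greater than or equal to 10 mg / l") and says of the laboratory results: "These results are based on examinations systematically performed in the newborn". It also says what counts as a clinical sign ("Any anomaly of the clinical examination that does not fit into evidence in another pathology will be considered as a sign of infection"), but uses clinical signs only for the *probable* class.

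Section 16.3 sets the effect measure for the primary and secondary outcomes: "The effects will be measured as relative risk, with their 95% confidence interval". Nothing elsewhere in the Protocol limits *certain* to central specimens or adds a clinical condition to it.

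**The concern.** The section separates peripheral from central cultures when it lists the data, then drops the distinction where it grades certainty. A newborn with a normal examination, a positive peripheral specimen, a negative central specimen and a CRP of 12 mg/l is *certain*, the same class as a newborn with a positive central specimen.

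A peripheral specimen may be positive because the newborn is colonised and not infected. If that happens about equally often in the two blinded arms, these newborns add the same number of events to each arm. The published rate of certain infection would then be too high, and any relative risk below 1 would be pulled toward 1. Because the results come from routine examinations, nothing in the text confines specimens to newborns who look ill.

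**Working it through.** **1. The plan's own figures.** The Protocol gives no rate for neonatal infection or for culture positivity, so there is no figure on this outcome to reproduce. The only design figure is 238 per group in section 16.1, for preterm delivery at 17% v 8.5%, α = 0.05 (taken as two-sided) and power 0.80. With unpooled variance:

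n = (1.96 + 0.84)² × (0.17×0.83 + 0.085×0.915) / 0.085² ≈ 7.85 × 0.2189 / 0.007225 ≈ 238.

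It reproduces. It serves below only as the number per arm.

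**2. Applying the definitions.** I read *certain* as (peripheral or central positive) and CRP >10 mg/l, and *probable* as (abnormal examination or chorioamnionitis) and CRP >10 mg/l.

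| Culture | Clinical sign or chorioamnionitis | CRP >10 | Class |
|---|---|---|---|
| central positive | no | yes | certain |
| peripheral positive only | no | yes | certain |
| either positive | yes | yes | certain |
| none positive | yes | yes | probable |
| peripheral positive only | no | no | uninfected |

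Rows 1 and 2 are the point: they fall in the same class. The definition has no brackets. On the other reading, a peripheral positive alone would be *certain* whatever the CRP, which would widen the mixture.

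**3. Size, under assumptions.** Assume true certain infection of 2% on placebo and 1% on josamycin (RR 0.50). Let f be the share of all newborns, equal in both arms, who are not infected but have a positive peripheral specimen and CRP >10.

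- Observed RR = (0.01 + f) / (0.02 + f)
- Share of the class that is not truly infected, both arms pooled = 2f / (0.03 + 2f)

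| f | placebo | josamycin | RR | pooled share |
|---|---|---|---|---|
| 0 | 2.0% | 1.0% | 0.50 | 0% |
| 0.1% | 2.1% | 1.1% | 0.52 | 6% |
| 0.25% | 2.25% | 1.25% | 0.56 | 14% |
| 1% | 3.0% | 2.0% | 0.67 | 40% |
| 2% | 4.0% | 3.0% | 0.75 | 57% |
| 4% | 6.0% | 5.0% | 0.83 | 73% |

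With true rates of 4% v 2%, the formula (0.02 + f) / (0.04 + f) gives 0.60, 0.67 and 0.75 at f = 1%, 2% and 4%.

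**4. Precision.** Take 238 newborns per arm and SE of ln RR = √(1/a − 1/238 + 1/b − 1/238), where a and b are the expected events.

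- f = 0: 2.38 v 4.76 events, SE 0.789, RR 0.50, 95% CI about 0.11 to 2.35.
- f = 2%: 7.14 v 9.52 events, SE 0.487, RR 0.75, 95% CI about 0.29 to 1.95.

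Neither interval would settle anything about this outcome.

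**The case against.** The strongest reply is that this is a deliberate case definition and not an error. The classes grade certainty, not severity. A culture plus CRP ranks above CRP plus a clinical sign without a culture, which is a coherent ladder. That stands. A reader might infer that the order of certainty is inverted, or that well newborns outrank sick ones. The text does not support this: a sick newborn with any positive culture and CRP >10 is also *certain*, and on the bracketed reading colonisation without a raised CRP never qualifies. But CRP >10 is equally required for *probable*, so it cannot explain why a peripheral positive ranks as high as a central one.

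Second, nothing in the Protocol says that a peripheral positive may mean only colonisation. That also stands. It is clinical reasoning, and f could be very small.

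Third, one might argue for equal false positives in both arms on the ground that section 12.2.2.2 names group B streptococci and *Escherichia coli* as the usual causes, while section 8 targets mycoplasmas. The same argument suggests that centrally confirmed infection may also be little affected by josamycin. If the true RR is 1, then (0.02 + f) / (0.02 + f) = 1 and nothing is diluted, although the rate is still inflated. The assumed 0.50 is therefore a favourable case for the concern.

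Fourth, the components are listed separately, so a central-only analysis stays possible. Whether the classes are pooled may be set in the analysis plan, which is not at hand. Both points lower the stakes. They do not change the definition that the Protocol fixes.

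**Conclusion.** The concern holds in a limited form. As defined, *certain* puts centrally confirmed infection together with peripheral culture plus raised CRP, and the Protocol gives no reason for treating them alike. Two consequences follow if some of the second group are not infected: the reported rate is too high, and, if their frequency is similar in both arms, a relative risk below 1 moves toward 1.

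The size cannot be taken from the documents. Under the assumed 2% v 1%, it runs from negligible (RR 0.52 at f = 0.1%) to substantial (0.83 at f = 4%). If josamycin altered peripheral positivity itself, the equal-frequency assumption would fail and the direction would be open.

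A reader might go further and conclude that the trial's result is at risk. It is not. Section 12.1 makes preterm delivery the primary criterion, the 238 per group rest on that alone, and at this sample size the infection outcome is uninformative under either definition. The point is worth correcting because the label *certain* would be misleading in a report and the correction is cheap.

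**What to change.** In section 12.2.2.2:

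1. Reserve *certain* for a positive central specimen, with the CRP criterion as now stated.
2. Place a positive peripheral specimen with CRP >10 mg/l and no positive central specimen in *probable*. Do not require a clinical sign or chorioamnionitis as well: newborns who have either, with CRP >10, are already *probable*, so such a rule would make the peripheral culture redundant and move the remaining newborns to *uninfected*.
3. Keep the existing clinical or chorioamnionitis route to *probable*.
4. Report the two classes separately and combined, with the number of newborns per arm who had a central specimen taken.
5. While editing, write the definitions with brackets and use one CRP cut-off; the parameter list counts a value of exactly 10 mg/l as positive and the class definitions do not.

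The cost is recoding of items already listed for collection, with no new test. There will be fewer *certain* events and a wider interval for that class. A newborn without a central specimen can no longer be *certain*, and the Protocol does not say how many that would be. Items 1 to 4 leave membership of the combined class unchanged, so any dilution there remains; the gain is a top class that means what its name says.

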13.3 Sending the sample to the bacteriology laboratory

The amniotic fluid samples for research (PCR for Mycoplasma hominis and Ureaplasma spp) will be stored at 4 ° C in a specific medium for a maximum of 3 days and delivered by the APHP coureur to the bacteriology laboratory. Cochin hospital where they will be received by the laboratory technician.

13.4 Selection of patients for the therapeutic trial

The result of the PCR will be transmitted the same day by fax to the investigating doctor (and the URC Henri Mondor).

If the PCR is negative, the patient will be informed of the result by telephone. The doctor will inform her that she will not participate in the therapeutic trial but that the follow-up of her pregnancy will be carried out in a traditional way and that the data collected during this follow-up will be used for research purposes (until delivery and her maternity leave). The patient will be reviewed by the investigating physician during scheduled visits as part of the normal follow-up of her pregnancy. Since no visit is done specifically for the research, it does not entail any additional cost for the patient.

If the PCR is positive for Ureaplasma spp. and / or Mycoplasma hominis, the patient will be contacted by the clinical research technician who will propose an appointment with the doctor to announce this result to him and propose him the batch of treatment.

The doctor will make sure that the patient is willing to continue the research and participate in the therapeutic trial.

If the patient does not wish to participate in the therapeutic trial, the patient will be out of the study. The monitoring of her pregnancy will be ensured according to the current practices of the service, and in the best interest for the patient and her future child.

If the patient wishes to continue her participation, an appointment will be offered for a treatment dispensation visit (if telephone contact). During this visit, the patient will be randomized in the group (Josamycin) or in the group (Placebo). Neither the doctors nor the patients will know in which group they belong. Patient travel expenses will be borne by the research sponsor.

3.5 Randomization and Treatment Administration

The randomization will be done according to a stratified randomisation list on the centers, prepared by the URC Henri Mondor.

The randomization will be done directly online from the cleanweb software.

The batch of treatment will then be given to the patient by the pharmacy, on a specific order of the investigator (Josamycin or placebo, at a dosage of 1 gram morning and evening orally for 10 days).

A blind survey card will be given to patients. (See chapter on the lifting of blindness)

The treatment batches will be distributed in the pharmacies of the investigative centers by the AGEPS. They will be labeled in accordance with the legislation in force for drugs intended for therapeutic trials. In order to guarantee blindness, josamycin or placebo treatment batches will look identical

13.6 Monitoring treatment adherence

A follow-up and patient recall procedure will be performed to monitor adherence to treatment. A telephone call-back will take place 15 days after the beginning of the treatment and will check with a short questionnaire the compliance and the absence of side effects related to the treatment (Appendix II)

The patient will also be asked to return the blank, opened or empty treatment pack at her next consultation. Consultation visits will be monthly until delivery. These boxes will be kept in the pharmacies of the centers until the end of the research.

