13.8 Patient follow-up

The follow-up of all PCR + / PCR- patients will be recorded under the responsibility of the investigator by the clinical research technician.

In order to check for possible confounding factors, data concerning the management, the evolution of pregnancy, delivery and the characteristics at birth of the newborn will be collected.

Maternal follow-up will be carried out until the maternity leave.

The follow-up of premature newborns will be carried out until a corrected age of 36 weeks.

The follow-up of the newborns will be realized until the exit of the maternity.

Data on pregnancy outcome after inclusion in the study will be collected.

Data regarding vaginal sampling between 35 and 37 weeks will be collected.

Data concerning the prescription of antibiotics during pregnancy will be collected.

Data on delivery and neonatal follow-up before leaving the maternity ward will be collected.

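### Section 16.3 compares adverse events and unblinding across all three groups, but the side-effect call reaches only randomised women, so adverse-event contrasts with PCR-negative women are open to ascertainment bias

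*Protocol*

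**What the plan says.** Section 13.6 (Monitoring treatment adherence) states that "A telephone call-back will take place 15 days after the beginning of the treatment" and that it "will check with a short questionnaire the compliance and the absence of side effects related to the treatment". For the women who received a treatment pack it adds: "Consultation visits will be monthly until delivery".

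Section 13.4 deals with PCR-negative women differently. They learn their result by telephone, do not enter the therapeutic trial, and are seen at the ordinary visits of their pregnancy: "Since no visit is done specifically for the research". PCR-positive women who decline the trial leave the study, so the two PCR-positive groups analysed are the josamycin and placebo arms.

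Section 13.8 applies to everyone: "The follow-up of all PCR + / PCR- patients will be recorded under the responsibility of the investigator by the clinical research technician". The items it then lists cover management, the course of pregnancy, delivery, the newborn, vaginal sampling and antibiotic prescriptions. Adverse events are not named there.

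Section 16.3 says: "The study will distinguish 3 groups of patients according to the studied factor and the prescription of an antibiotic treatment". The groups are PCR-negative, PCR-positive without antibiotic and PCR-positive with antibiotic, each to be compared with the others. The items collected during pregnancy are "number of consultations, treatment, concomitant treatments, protocol outputs, adverse events and unblinding". A separate intention-to-treat comparison of placebo with josamycin follows, for the main endpoint and the secondary criteria.

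**The concern.** An adverse-event comparison between groups is interpretable only if events are sought in the same way in each. Here two groups are telephoned and asked about side effects, and the third is not. A difference from the PCR-negative group could then reflect the asking, yet be read as harm from the infection or from the tablets. Because the PCR-negative group is very large, a moderate difference in capture could reach statistical significance.

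Unblinding is a simpler problem: PCR-negative women receive no blinded treatment, so the item has no meaning for them.

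The placement in 16.3 matters. The intention-to-treat step covers the main endpoint and the secondary criteria, and section 12.2 does not list adverse events among the latter. In the text available, the three-group list is therefore the only place where an adverse-event analysis is specified, and josamycin versus placebo appears only as one pair within it.

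**Working it through.** **Step 1. Who is asked, and who is compared.**

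| | PCR-negative | Placebo | Josamycin |
|---|---|---|---|
| Side-effect call at day 15 (13.6) | no, no treatment start to count from | yes | yes |
| Visits | routine only (13.4) | dispensation visit, then monthly (13.4, 13.6) | same as placebo |
| Follow-up recorded (13.8) | yes | yes | yes |
| Blinded treatment that could be unblinded | no | yes | yes |
| In the 16.3 comparison of adverse events and unblinding | yes | yes | yes |

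The first and last rows do not match for PCR-negative women. The two randomised columns are identical.

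**Step 2. Group sizes.** Section 16.1 gives 238 per arm for 17% against 8.5% (a 50% reduction), α = 0.05 and power 0.80. With unpooled variance and a two-sided test:

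n = (1.960 + 0.842)² × (0.17 × 0.83 + 0.085 × 0.915) / 0.085² = 237.8, so 238 per arm.

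The plan's figure is reproduced and is not in question; it serves only as an input. Randomised women: 2 × 238 = 476. PCR-negative women: 3200 × (1 − 0.15) = 2720. Since 16.1 puts the prevalence at 15% or more, 2720 is an upper figure.

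**Step 3. Illustration of the bias.** The protocol gives no adverse-event rate and no capture rate, so everything in this step is assumed: the same true risk r in all groups (10% or 20%), capture of 90% in women who are called, and capture c of 90%, 60% or 30% in PCR-negative women.

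Apparent ratio = (r × 0.90) / (r × c) = 0.90 / c. The true risk cancels.

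- c = 90%: ratio 1.0
- c = 60%: ratio 1.5
- c = 30%: ratio 3.0

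Chance of a falsely significant difference (two-sided 5%, one arm of 238 against 2720). Let a = 0.90r, b = c × r, p = (238a + 2720b)/2958, SE₀ = √[p(1 − p)(1/238 + 1/2720)] and SE₁ = √[a(1 − a)/238 + b(1 − b)/2720]. For a > b the probability is approximately Φ[(a − b − 1.96 SE₀)/SE₁].

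Example, r = 10% and c = 60%: a = 0.09, b = 0.06, p = 0.0624, SE₀ = 0.0164, SE₁ = 0.0191. Then (0.03 − 0.0321)/0.0191 = −0.11, which gives 46%.

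| Capture in PCR-negative | Ratio | r = 10% | r = 20% |
|---|---|---|---|
| 90% | 1.0 | 5% | 5% |
| 60% | 1.5 | 46% | 74% |
| 30% | 3.0 | 97% | about 100% |

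**Step 4. The randomised contrast.** Capture is the same in both arms because the call is the same and 13.4 keeps doctors and patients blinded. With equal true risk the josamycin-to-placebo ratio is (r × 0.90)/(r × 0.90) = 1.0 in every row.

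**The case against.** The strongest reply is that 13.6 concerns adherence and is not the adverse-event section. The text available passes from 13.9 to 16.1, and Appendix II (the questionnaire) is not shown, so rules for recording adverse events in all included women may well exist. PCR-negative women are seen by the investigating physician and their follow-up is recorded, so near-equal capture is possible. This stands as far as the size of the bias goes: nobody can say from these documents that the call is the only source of adverse events, and the ratio may be 1.0. It does not remove the point, because an additional solicitation confined to randomised women remains unequal whatever common recording exists beside it.

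A second reply is that the 16.3 list plainly contains items that cannot apply to PCR-negative women, such as treatment and unblinding, and so describes the course of pregnancy rather than setting up a formal safety test. That is a fair reading and is why the point is minor. But 16.3 says that the groups are compared with each other and does not say which items apply to which groups.

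Four stronger inferences are tempting and are not supported:

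- *The whole adverse-event comparison measures ascertainment rather than safety.* Only contrasts with PCR-negative women are exposed; josamycin versus placebo is not.
- *PCR-positive women will certainly show more events.* If the questionnaire's focus on treatment-related effects lowered capture in called women to, say, 45% against 60% in routine notes, the ratio would be 0.45/0.60 = 0.75. Even the direction is not fixed.
- *Drug-caused events that resemble pregnancy symptoms are lost.* This depends on a questionnaire that is not shown. Nothing available says who judges relatedness or what is discarded.
- *The consultation count differs by at least one visit by design.* The documents do not say whether the dispensation visit counts as a consultation or can coincide with a routine one.

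**Conclusion.** The concern holds in a limited form. Section 16.3 specifies an adverse-event comparison that includes a group which, in the text shown, does not receive the side-effect call given to the other two, and it lists unblinding for women to whom it cannot apply. Contrasts of either randomised arm with PCR-negative women are therefore open to ascertainment bias of unknown size. On the assumed capture rates the apparent ratio runs from 1.0 (equal capture) through 1.5 to 3.0 with no true difference; these figures illustrate sensitivity and are not estimates. The josamycin-placebo safety contrast, the primary endpoint and the randomised efficacy comparison are not affected. This is a minor point, worth correcting because the correction costs almost nothing.

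**What to change.** In section 16.3, restrict the comparison of adverse events, unblinding and treatment-related protocol exits to josamycin versus placebo. Keep the three-group comparison for baseline data and for pregnancy-course items collected identically in all women. This is a change of wording only.

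Optionally, if Appendix II and the adverse-event section do not already provide for it, word the question in the existing call so that all untoward events since the start of treatment are recorded, with relatedness assessed separately while still blinded. The cost is slightly more data entry for about 476 women; no extra contact is needed.
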